### Study Procedure

The overview of the data collection process is shown in Figure 2. Each participant is first invited to attend a mandatory prestudy session. During this session, participants are required to sign an informed consent form, which articulates the purpose of the study, the data collection procedure, and data confidentiality protocols. Subsequently, members of the research team provide device training for the wrist-worn biosensor (Empatica Embrace Plus) and GPS tracker (Qstarz BL 1000ST) carried in a bag or pocket. Training includes hands-on practice with proper device use, charging procedures, and a review of common issues. Participants should demonstrate competency in device operation before leaving the session. Following device training, participants are asked to complete a Short Form-12 (SF-12) Health Survey assessing their mental health over the past 4 weeks, along with their environmental perceptions and sociodemographic information. Upon completion, participants receive initial incentives of HKD $100 (US $12).

**Figure 2 figure2:**
[figure not shown]
Overview of data collection process.

During the 7-day experimental period, participants are required to wear the biosensor for a minimum of 18 hours daily and carry the GPS tracker during all outdoor activities for at least 1 hour per day. This duration is based on prior theory indicating that valid accelerometer data requires a minimum of 3 days with at least 10 hours of daily wear time [26]. Wear time is defined as the period when the device is properly worn and collecting valid data. The biosensor uses on-skin detection algorithms to automatically identify and filter the data recorded while not being used as intended, reducing the likelihood of including unreliable observations [27]. After each day of activities, participants are asked to complete a questionnaire. Daily reminder text messages are sent to ensure questionnaire completion. In case of technical issues or device-related problems, participants are advised to contact the research team by phone for immediate assistance, including device charging support.

Upon completion of the 7-day experiment, participants are asked to complete an exit interview including: (1) the SF-12 questionnaire to assess their mental health during the study week, (2) an exit survey covering study feedback and retrospective behavior, and (3) a questionnaire assessing their perceived built environment based on their daily activity spaces. Participants who can successfully provide at least 5 days of data from both biosensor and GPS devices could receive full incentives of HKD $400 (US $50). If data quality does not meet the criteria, a one-time make-up experiment is offered.

### Digital Biomarkers Associated With Mental Health

Participants’ mental health is measured by a wrist-worn biosensor, a physiological monitoring device that captures an individual’s motion-based activity, blood volume pulse (BVP), and skin temperature and links them to physiological signals (Table 1). Skin conductance is measured in microsiemens (μS) and ranges from 2-100 μS. The sampling rate is 4 Hz. Electrodermal activity (EDA) explorer will be used to detect peaks in 5-second periods of the clean electrodermal 5-minute signal. The biosensor also assesses acceleration and rotation (actigraphy) and BVP by photoplethysmography (PPG) at sampling rates of 64 Hz, as well as peripheral (skin) temperature at sampling rates of 1 Hz.

**Table 1 table1:** Measurements for raw sensor data used in this study and their relationships with mental health.

High-frequency sensor data	Measurement method	Sampling rate	Pathway to mental health outcomes	Connection to mental health outcomes
EDA^a^	Skin conductance	4 Hz	Sympathetic nervous system activation	Higher EDA indicates increased stress and emotional arousal
BVP^b^	PPG^c^	64 Hz	Cardiovascular regulation	Irregular patterns reflect anxiety and stress states
Skin Temperature	Infrared sensor	1 Hz	Peripheral vasoconstriction	Decreased peripheral temperature indicates sympathetic nervous system activation during stress
Activity (actigraphy)	3-axis accelerometer	64 Hz	Physical activity patterns	Regular physical activity promotes positive mental health through various physiological and psychological pathways

^a^EDA: electrodermal activity.

^b^BVP: blood volume pulse.

^c^PPG: photoplethysmography.

In subsequent analysis, these raw sensor data will be processed into minute-level digital biomarkers through Empatica’s proprietary algorithms, which have been validated through prospective clinical studies sponsored by Empatica [28,29]. The digital biomarkers are aggregated into 1-minute windows, including EDA (0.01-100 μS), pulse rate (24-240 beats per minute [bpm]), skin temperature (28 °C-35 °C) as primary outcomes, as well as pulse rate variability (PRV, root-mean-square of successive difference [RMSSD] up to 300 ms), and respiratory rate (6-60 breaths per minute) as secondary outcomes. Sleep detection is also monitored, with periods categorized as awake, sleep, or interruption. All these digital biomarkers will be computed and aligned at 1-minute intervals using specific aggregation methods for each indicator.

Individual baseline values are measured in two phases. First, during the preinterview session, participants wear the biosensor device while completing preinterview survey, which typically takes more than 10 minutes in a quiet environment. These measurements during the survey completion period serve as their initial baseline. Second, during the study period, we identify the daily baseline for each participant by selecting the 15-minute continuous period when their EDA levels are at their lowest, given that EDA is a primary indicator of sympathetic nervous system activation and stress response [30]. During these periods, we also record corresponding pulse rate, respiratory rate, and skin temperature values. These daily baseline values will be averaged across multiple days to establish a personalized baseline.

### Physical Activity and Mobility Measurements

Physical activities are measured using accelerometer data from both biosensor and GPS devices. The biosensor device captures raw accelerometry data through its integrated 3-axis accelerometer at 64 Hz sampling rate. Using proprietary machine learning algorithms, the accelerometry signals are processed into minute-level digital biomarkers, including activity counts (0-200 counts), activity intensity levels (categorized as sedentary, low, moderate, or vigorous), movement classification (still, generic, walking, or running), step counts (up to 192 steps), and metabolic equivalent of task (MET, 0.95-8.53).

Raw GPS data are collected with 1-second sampling intervals. Table 2 listed each measurement, sample resolution, and aggregation process. The GPS device logs geographic coordinates, distance, speed, elevation, and time. In subsequent analysis, GPS data (1-second intervals) will be aligned with the biosensor data at 1-minute intervals. Within each 1-minute window, all GPS location points will be retained rather than aggregating to a single point. This approach maintains detailed movement patterns and allows precise assessment of environmental exposures.

**Table 2 table2:** Measurement of digital biomarkers and location indicators at 1-minute resolution.

Indicator	Raw sampling	Aggregation method	Output interval	Range	Resolution
Activity counts	64 Hz (accelerometer)	Zeros-crossing count in filtered data	1 minute	0-200 counts	1 count
Activity intensity	Derived from MET^a^	MET threshold categorization	1 minute	4 categories (sedentary, low physical activity, moderate physical activity, or vigorous physical activity)	Categorical
Activity classification	64 Hz (accelerometer)	3-second nonoverlapping windows aggregation	1 minute	4 categories (still, generic, walking, or running)	Categorical
Step counts	64 Hz (accelerometer)	Step detection from accelerometer data	1 minute	0-192 steps	1 step
EDA^b^	4 Hz	Average over window	1 minute	0.01-100 μS	~55 pS
MET	64 Hz (accelerometer)	Energy expenditure calculation	1 minute	0.95-8.53 MET	—^c^
Pulse rate	64 Hz (PPG^d^)	Aggregation of 10-second windows	1 minute	24-240 bpm^e^	1 bpm
PRV^f^ (RMSSD^g^)	64 Hz (PPG)	RMSSD calculation from interbeat intervals	1 minute	0-300+ ms	0.000001 ms
Respiratory rate	64 Hz (PPG)	Combining 30-second windows	1 minute	6-60 brpm^h^	1 brpm
Skin temperature	1 Hz	Average over window	1 minute	0 °C-85 °C	0.01 °C
Sleep detection	Derived from activity counts	Activity analysis for sleep/wake periods	1 minute	0 (awake), 101 (sleep), 102 (wake), 300 (interruption)	Categorical
GPS location data	1 second	Total area covered by multiradius buffers around sequential points within 1-minute window	1 minute	0-1 km²	0.0001 km²

^a^MET: metabolic equivalent of task.

^b^EDA: electrodermal activity.

^c^Not applicable/Not available.

^d^PPG: photoplethysmography.

^e^bpm: beats per minute.

^f^PRV: pulse rate variability.

^g^RMSSD: root-mean-square of successive difference.

^h^brpm: breaths per minute.

### Environmental Exposure Measurements

We will measure the built environment from multiple perspectives. Primary environmental exposures include air pollution (particulate matter ≤2.5 µm [PM2.5], nitrogen dioxide [NO_2_], and air quality index [AQI]), urban density (ground coverage ratio [GCR] and street coverage ratio [SCR]), and green-blue space access (normalized difference vegetation index [NDVI] and eye-level exposure metrics). Secondary environmental assessments comprise mobility barriers, land use mix, road accessibility, and thermal environment.

Air pollution exposure will be evaluated by PM2.5, NO_2_, and AQI from Hong Kong’s 18 air quality monitoring stations operated by the Environmental Protection Department. Kriging or inverse distance weighting methods will be applied to estimate air pollution levels across the study area. Urban density will be quantified using GCR and SCR for each trajectory buffer area. GCR represents the ratio of total building footprint to buffer area, while SCR indicates the percentage of vehicular street coverage. Green-blue space exposure will be quantified using multiple methods. Greenspace availability will be measured by NDVI from Sentinel-2 satellite imagery (10-meter resolution). Eye-level exposure to green space, recreational areas, blue spaces, and public spaces will be evaluated using Google Maps Street view images [31,32], which will be newly acquired during the analytical process in 2026.

For secondary environmental assessments, mobility barriers will be assessed by analyzing street intersection density, obstacles, slopes, surface conditions, traffic black spots (ie, high-risk areas for accidents), and barrier-free facilities (eg, ramps, staircases, footways, lifts). These factors will be derived from government infrastructure data and 3D pedestrian network datasets within a defined radius of each GPS position. Land use mix will be quantified by the Shannon entropy index [33] from government land use raster files. Point of interest (POI) density will be computed through kernel density estimation of geocoded points from government POI databases. Road accessibility will be calculated using degree, closeness, and betweenness centrality measures will be derived from graph theory algorithms [34]. Furthermore, the thermal environment will be assessed through land surface temperature, which will be retrieved from Landsat 8 thermal infrared sensor bands using the split-window algorithm and atmospheric correction techniques.

Dynamic environmental exposure will be calculated using kernel density estimation (KDE) at multiple temporal scales based on GPS trajectories [35,36]. Specifically, we will analyze exposure at the minute level, daily level, and weekly level. This multiscale approach allows us to examine both acute and cumulative environmental exposures in relation to physical activity patterns and stress responses. It distinguishes between acute high-intensity exposures at the minute level and sustained low-intensity exposures over longer periods, which may produce equivalent cumulative values but represent distinct exposure patterns across the study period. The KDE-derived exposure surface will be integrated with environmental variables to create composite exposure metrics, which will then be temporally aligned with accelerometer-derived activity data and physiological measurements. For example, minute-level environmental exposure can be directly linked to concurrent physical activity intensity and MET values, while daily and weekly exposure metrics can be associated with aggregate activity patterns and cumulative physiological responses.

For the overall measurement of built environment characteristics and exposure metrics, we will perform index normalization across all environmental indicators, as these measures are originally on different scales (eg, NDVI ranges from –1 to 1, while AQI ranges from 0 to 500). Each environmental indicator will be transformed to a standardized scale (0-1) while maintaining their relative distributions, supporting both within-subject comparisons of different environmental exposures and between-subject comparisons of exposure patterns.

### Self-Report Measures and Covariates

In addition to objective measurements (eg, GPS-recorded location and biosensor-derived biomarkers), subjective measurements were collected through structured questionnaires at 3 time points: pre-experiment, during-experiment, and postexperiment. The questionnaires are provided in both English and Cantonese, allowing participants to choose their preferred language.

The preinterview questionnaire contained health-related quality of life assessment using SF-12, which evaluates both physical and mental health components, health behaviors including smoking and alcohol consumption patterns, and perceived built environment quality. The built environment perception was assessed through 3 domains regarding public service accessibility, public open space and green space quality, and transportation convenience. These items were measured on a 5-point Likert scale from 1 (strongly disagree) to 5 (strongly agree). Weather perception and comfort assessment were also included.

During the experiment, participants completed daily surveys recording their travel modes, activity locations and types, estimated phone screen time, and clothing combinations. Emotional states were assessed using a modified version of the Positive and Negative Affect Schedule, comprising 10 mood items rated on Likert scales [37].

At the end of the experiment, participants completed an exit interview reflecting on their experiences over the 7-day experimental period. The interview assessed mental health using the Patient Health Questionnaire for depression symptoms, and health behaviors through detailed alcohol consumption and smoking patterns (frequency, quantity, and motivations). Environmental perceptions and mood responses to different environments were evaluated, including emotional responses to various urban settings such as public gardens, waterfront promenades, urban streets, and mountain trails. Overall device experience and weather comfort preferences were also assessed. These subjective measurements complement our objective data by capturing perceptions and experiences that cannot be recorded by GPS devices or biosensors.

Demographic covariates include age, gender, height (cm), weight (kg), education level, marital status, occupation status, housing type, length of residence in Hong Kong (years), living conditions, monthly household income (excluding welfare or disability allowances), household size (including the participant but excluding foreign domestic workers), residential area in Hong Kong, and building of residence.

### Data Processing and Analysis

GPS data (recorded at 1-second intervals) and physiological data from the biosensor will be temporally aligned at 1-minute intervals. To explore the relationship between environmental exposure and mental health, descriptive statistics will be computed for all variables, including biomarkers and demographic characteristics collected from biosensors and survey data. Diagnostic statistics will be applied to assess model adequacy. Outcome variables (eg, biomarkers) will be log-transformed when necessary to better approximate Gaussian distribution for residuals.

Environmental exposure will be quantified by applying kernel weights to the GPS data. This method accurately measures the precise exposure at the GPS point level, with a proximity-weighted raster surface at fine granularity (50 m × 50 m) will be constructed for the activity space of each individual [38]. For each grid cell, exposure values will be calculated based on kernel density estimation, with weights proportional to the time spent in each location.

To analyze the relationship between these environmental exposures and physiological responses, we will use multiple analytical approaches. Statistical testing will follow a hierarchical approach with α=.01 for primary analyses examining the 9 prespecified associations (3 environmental exposures × 3 digital biomarkers) and α=.05 for secondary analyses. Generalized linear mixed models will serve as our primary method to examine the direct relationships between GPS-derived exposure measures and biomarker variations, accounting for individual differences through random effects. To capture potential nonlinear relationships, we will use generalized additive mixed models. These models will be enhanced with time-series analysis techniques, including autoregressive integrated moving average models to examine temporal patterns and cross-correlation functions to identify potential lag effects between environmental exposure and physiological responses. This analytical framework allows us to understand both the immediate and delayed effects of environmental exposure on physiological responses, while accounting for individual variations and temporal dynamics.

Structural equation modeling will be used to investigate the mediating role of physical activities between environmental exposure and mental health. It accounts for both observable and latent variables, particularly mental health as measured by the SF-12 questionnaire. To further explore the spatiotemporal variation in the relationship between environmental exposures and mental health changes, geographically and temporally weighted regression will be used, which extends traditional geographical weighted regression by incorporating both spatial and temporal dimensions, revealing the varying relationships across space and time. This approach captures dynamic patterns of environmental exposure influences on mental health status across different locations and temporal periods.

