Traditional measurement using questionnaire surveys has been found time- and labor-consuming [15,16], and self-reported instruments are subject to individual characteristics and preferences [17,18]. Recent studies have increasingly adopted wearable devices, allowing for continuous monitoring of physiological parameters and real-time assessment of physical and mental health conditions [19-22].

In this study, we aim to investigate the association between changes in environmental exposure, including green and blue space and walkability, and changes in biomarkers associated with mental health by using minute-level GPS-based environmental measurements and wrist-worn biosensors (Figure 1). Primary analyses will examine associations between 3 environmental exposures (air pollution, urban density, and green-blue space access) and 3 digital biomarkers (electrodermal activity, pulse rate, and skin temperature). Secondary analyses will investigate physical activity metrics and explore questionnaire responses and additional environmental assessments, including walkability, mobility barriers, land use mix, road accessibility, and thermal conditions.

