### Participants’ Recruitment

This study adopts a mixed methods approach, combining quantitative and qualitative methods with a cross-disciplinary approach. For sampling strategy, we apply a predefined approach by integrating stratified random sampling with multistage sampling methodologies. Initially, we categorize small territorial planning units (STPUs) in Hong Kong based on two indicators: (1) percentage of older adults (aged ≥65 years) using Hong Kong Census data: this serves as a proxy for age-specific demographic composition in each STPU, indicating areas with aging population densities and their corresponding service demands (eg, health care facilities and community support infrastructure) [23]; and (2) proximity to the nearest green space using OpenStreetMap: this indicator calculates the walking time from an STPU centroid to the nearest urban or country park, representing a crucial environmental factor for physical activities and recreation across all age groups. We further categorize STPUs into low, median, and high groups using terciles for each indicator: (1) Percentage of older adults: low (3.58%-15.78%), medium (15.78%-20.79%), and high (20.79%-65.76%); and (2) proximity to nearest park: low (8.72-56.00 minutes), medium (3.86-8.71 minutes), and high (0.10-3.85 minutes). Finally, we select STPUs based on indicator combination (percentage of older adults–proximity to green space in minutes): high–high (n=32), high–low (n=14), low–high (n=11), and low–low (n=40).

The target sample size of 750 is based on the current Hong Kong population size of 7.4 million. The sample size represents approximately 1 out of 10,000 of the population, which is a common patient representation in a mid-sized region [24,25].

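### The primary mixed model as described does not separate within-person from between-person association, although the aim is to relate changes in exposure to changes in biomarkers; this matters most for daily and weekly exposure

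*Protocol article*

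**What the plan says.** All references are to the Protocol article.

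- **Aim (Introduction).** The study will "investigate the association between changes in environmental exposure, including green and blue space and walkability, and changes in biomarkers associated with mental health", using minute-level GPS measurements. The same section criticises earlier work for stationary bias, that is, for judging exposure by where people live.
- **Primary model (Data Processing and Analysis).** Generalized linear mixed models are the "primary method to examine the direct relationships between GPS-derived exposure measures and biomarker variations, accounting for individual differences through random effects". The testing level is "α=.01 for primary analyses examining the 9 prespecified associations (3 environmental exposures × 3 digital biomarkers").
- **Exposure scale (Environmental Exposure Measurements).** Each indicator is rescaled to 0-1 in a way that keeps its relative distribution, "supporting both within-subject comparisons of different environmental exposures and between-subject comparisons of exposure patterns".
- **Time scale (same section).** Exposure will be analysed by minute, day and week. No section says which scale carries the nine primary tests.
- **Hypotheses (Anticipated Findings).** Both kinds are stated: responses while a person is exposed, and lower baseline stress in people with more cumulative green exposure.

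**The concern.** A random intercept is assumed to be unrelated to exposure. If people who spend time in greener or denser places also differ in their usual biomarker level, that difference enters a single exposure coefficient along with the person's own responses. The test then asks whether a weighted combination of the two slopes is zero. It can reject when nobody's biomarker moves with their own exposure.

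At stake is what a significant primary result means. The study wants to move beyond comparing people by place of residence, and a blended coefficient can bring that comparison back unnoticed. The 0-1 rescaling does not help, because it applies to the indicator as a whole and leaves differences between people in place.

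**Working it through.** **The plan's own figure.** The article gives no power or error-rate figure. Its only sample-size statement is a population fraction: 7,400,000 / 10,000 = 740, against the stated 750. That agrees to about 1% but has no bearing on this point.

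**Inputs from the article.** N = 750; alpha = .01 per test (two-sided assumed, as the article does not say). Repeated values per person, T: 1 for a week; 7 for days; at least 7 × 60 = 420 minutes from the minimum GPS hour per day; up to 7 × 18 × 60 = 7,560 minutes from biosensor wear time (Study Procedure).

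**Assumptions, not in the article.** Share of exposure variance between persons 0.5 (also 0.8); share of biomarker variance between persons 0.5; correlation r between a person's usual exposure and usual biomarker level 0.1 to 0.5; true within-person slope zero.

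**Formulas** (random intercept, one uncentred exposure term, total variances set to 1):

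- Within information: W = N(T − 1) × var_W(x) / σ_e²
- Between information: B = N × var(x̄) / (σ_u² + σ_e²/T), with var(x̄) = var_B(x) + var_W(x)/T
- Weight on the between-person slope: w = B / (W + B)
- Between-person slope: b = r × √(var_B(x) × σ_u²) / var(x̄)
- Expected coefficient w × b; standard error 1/√(W + B); rejection when |Z| > 2.576

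**Daily level, T = 7, 50% shares.** W = 750 × 6 × 0.5/0.5 = 4,500. B = 750 × 0.571/0.571 = 750. So w = 750/5,250 = 14.3%. At r = 0.3, b = 0.15/0.571 = 0.2625, the coefficient is 0.0375, the standard error is 0.0138 and the ratio is 2.72, which gives 56% rejection.

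**Minute level, T = 420, independent errors, 50% shares.** W = 750 × 419 = 314,250 and B = 750, so w = 0.24%. At r = 0.3 the ratio is 0.40, which gives 1.6%.

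| Level | Exposure share between | w | r = 0.1 | r = 0.3 | r = 0.5 |
|---|---|---|---|---|---|
| Day (T = 7) | 0.5 | 14.3% | 4.8% | 56% | 97% |
| Day (T = 7) | 0.8 | 37.7% | 15% | 98% | 100% |
| Minute (T = 420) | 0.5 | 0.24% | 1.1% | 1.6% | 2.9% |
| Minute (T = 420) | 0.8 | 0.94% | 1.3% | 3.8% | 10.6% |
| Minute (T = 7,560) | 0.5 | 0.01% | 1.0% | 1.0% | 1.1% |

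With equal shares w is exactly 1/T. At the weekly level T = 1, so W = 0 and w = 1: the coefficient is entirely between-person.

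**Simulation check.** With T = 7 and 50% shares, the uncentred model rejected in 5.0%, 57% and 98% of runs at r = 0.1, 0.3 and 0.5. With exposure centred on the person mean, rejection was 0.75-1.5% at T = 7, 0.6-1.4% at T = 60 and 0.2-2.0% at T = 420. That is the nominal 1% within simulation noise.

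**Serial dependence at the minute level.** With first-order autoregressive errors in the model, T = 420 and 50% shares, most combinations tried gave 1-7%. The exceptions had slowly varying exposure. Exposure lag-1 correlation 0.99 with error lag-1 0.9 gave 6% at r = 0.3 and 21% at r = 0.5. Exposure lag-1 0.999 with error lag-1 0.9 gave 53% and 97%; with T = 2,520 that last case fell to 4% and 12%.

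**Sampled areas.** The selected planning units, by older-adult share and park proximity, are "high–high (n=32), high–low (n=14), low–high (n=11), and low–low (n=40"). Among units with a high older-adult share, 32/46 = 70% are close to a park, against 11/51 = 22% of units with a low share. The odds ratio is (32 × 40)/(14 × 11) = 8.3 and phi is 0.48.

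**The case against.** The other side has several good arguments.

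- **The article does not say that exposure enters uncentred.** This stands. Centring is a detail that an article may leave to the full plan, and its absence alone would be no finding. What the article does state is a change-on-change aim, random effects as the means of handling individuals, and a rescaling meant to serve both kinds of comparison. Together these leave open which comparison the nine tests address.
- **The objective is minute-level, where the problem is small.** This largely stands. The between weight is about 1/T. Yet daily and weekly analyses are also planned, and nothing confines the nine tests to minutes.
- **Between-person contrasts are wanted too.** True, and it argues for two reported coefficients, not one blend.
- **Covariates and a personal baseline exist.** Age, income and residential area are listed, and a low-EDA baseline is computed for each person. Their use in the primary model is not described. Covariates adjust only for what is measured, and a biomarker baseline does not centre exposure.
- **The area counts prove little.** This stands. They count areas, not participants, and park walking time is not NDVI, pollution or density. They show only that area age and park proximity are linked among the selected units.

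A reader might infer that the primary results could come wholly from who lives where. The article does not support that for minute-level analysis with many effectively independent minutes.

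**Conclusion.** The point holds in limited form. The primary model as described does not separate the two associations, while the stated aim concerns one of them. With no within-person effect, the chance of a significant result at alpha .01 is usually 1-4% with 420 independent minutes (10.6% at the extreme of the assumed range). It is higher for slowly varying exposure with modelled serial dependence. With seven daily values it runs from about 5% to 97% at 50% variance shares. A weekly coefficient is between-person only.

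The article supplies no variance shares or correlations, so these rates show what could happen and do not predict this study's results. This is a cheap improvement to the method, not evidence that the planned results will be wrong.

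**What to change.** In Data Processing and Analysis, state that in minute- and daily-level models each exposure enters as two terms: the person's own mean and the deviation from it. Base the nine alpha = .01 change-on-change tests on the deviation coefficient. Report the person-mean coefficient separately, for the cumulative, between-person hypothesis in Anticipated Findings. Label weekly-level results as between-person associations, and name the time scale on which the nine tests are made.

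The cost is a few sentences and one derived variable per exposure. Analysis is expected to run to June 2027, so the change can still be fixed in advance. The downside is that between-person information no longer adds precision to the primary test. At T = 7 with 50% shares the standard error grows by √(5,250/4,500) = 1.08, or 8%; with an 80% exposure share by √(2,887.5/1,800) = 1.27, or 27%. At T = 420 with 50% shares it grows by √(315,000/314,250), about 0.1%.
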